### Outcomes

Primary outcomes are changes from baseline in the composite score of all neuropsychological tests for cognition and in the average thickness of the retinal nerve fiber layer of each eye, as assessed by optical coherence tomography (OCT). As secondary cognitive outcomes, we will analyze composites for different cognitive domains, including memory, language, perception, and frontal functions (for further detail, please see section Cognitive Testing); assess the incidence of AD according to NINCDS-ADRDA criteria (McKhann et al., 1984); and evaluate the incidence of MCI, defined by Petersen’s diagnostic criteria (Petersen et al., 2001). Secondary OCT outcomes are macula cube thickness, cube volume, and central thickness.

Other secondary outcomes for the whole cohort are changes in anthropometric measures, lipid profile, serum inflammatory and oxidative stress markers, red blood cell (RBC) fatty acids, and urinary polyphenols. At the BCN site, the following secondary outcomes will be assessed: structural and functional brain MRI variables, carotid intima-media thickness (IMT) and plaque burden, body composition, bone mineral density, 24-h ambulatory blood pressure, leukocyte telomere length, and serum miRNAs.

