## Methods

### Study Design

The WAHA study is a dual center, single blind, randomized 2-year clinical trial conducted in free living, cognitively healthy elderly individuals^1^. The study is carried out in two centers: Loma Linda University, CA, USA (LLU) and Hospital Clínic, Barcelona, Spain (BCN). With a parallel design, participants were randomized to either the walnut group (consuming walnuts daily) or control group (abstaining from walnuts). Otherwise participants followed their habitual diet throughout the study. Primary aims are to assess changes in cognitive function and retinal integrity. Secondary aims relate to effects on cardio-metabolic risk factors, body weight and composition, and circulating markers of oxidation/inflammation. Additional secondary aims (BCN center) are changes in brain magnetic resonance imaging (MRI), ultrasound-assessed carotid atherosclerosis, blood pressure by 24-h ambulatory monitoring, bone mineral density, leukocyte telomere length, and microRNAs (miRNAs) related to lipoprotein metabolism.

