##### Cognitive testing

A comprehensive neuropsychological test battery evaluating several cognitive domains was administered at baseline and at the end of the trial. Neuropsychologists who were masked to participant’s group assignment conducted the cognitive tests. The instruments used were Block design from the Wechsler Adult Intelligence Scale (WAIS III) (Wechsler, 1997), Rey-Osterrieth Complex Figure (ROCF) (Rey, 1941), Rey Auditory Verbal Learning Test (RAVLT) (Rey, 1958), Boston Naming Test (Kaplan et al., 2001), Semantic category evocation of animals (Ramier and Hécaen, 1970), Number location and incomplete letters from the Visual Object and Space Perception Battery (VOSP) (Warrington and James, 1991), Trail Making Test, parts A and B (Partington and Leiter, 1949), Phonemic fluency (FAS) (Benton and Hamsher, 1976), Stroop Color Word Test (Stroop, 1935), Symbol Digit Modalities Test (SDMT) (Smith, 1973), Digit span forward and backward from the WAIS III (Wechsler, 1997), and the Conners Continuous Performance Test (CPT II) (Conners and Staff, 2000).

Subjects’ raw test punctuations were standardized to *z* scores to generate a global cognition composite by computing the mean standardized changes of all neuropsychological tests. This composite was pre-specified as the primary outcome of the study. Moreover, composites of cognitive domains analyzed separately were calculated. First, the memory composite included the mean standardized individual change scores of the RAVLT (immediate and delayed recall) and the 3-min recall of ROCF. Language composite included scores from animal semantic fluency and the Boston Naming Test. Perception composite included scores from number location and incomplete letters from VOSP battery and block design from WAIS-III battery. Finally, a composite score related to frontal functions was created including scores from TMT parts A and B, FAS, Stroop, SDMT, digit span from WAIS-III, and CPT-II. As secondary outcomes, composites assessing cognitive domains separately were defined.

In addition, information about cognitive reserve and mood was collected using a cognitive reserve questionnaire (Solé-Padullés et al., 2009) and the Hamilton Depression Rating Scale (Hamilton, 1967), respectively. Premorbid intelligence was assessed with the American National Adult Reading Test (Grober and Sliwinski, 1991) at LLU site and the Word Accentuation Test (Del Ser et al., 1997) at BCN site.

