### Statistical Analyses

Sample size calculation was based on prior results from the PREDIMED study (Valls-Pedret et al., 2015). We used as reference the 2-year unadjusted changes in RAVLT (total learning) scores in the Mediterranean diet enriched with nuts compared to the control diet. In order to have a 90% power to detect differences in the contrast with the null hypothesis, assuming mean changes of 1.05 and 2.10 points in the control and intervention groups, respectively, with a standard deviation of 4.00, the total number of participants required was 308 per group. Considering an estimated dropout rate of 10%, we needed to include a total of 686 participants.

All data collected in the study were entered into an online database (Onto CRF, Costaisa, Spain) managed for both centers. An oversight committee blinded to subject allocation monitored safety, quality of data collected, and trial’s progress.

Between-group differences in baseline neuropsychological and ophthalmologic data will be examined by ANOVA and further by ANCOVA adjusting for center, sex, age, education years, *APOE4* genotype, smoking, BMI, energy intake, physical activity, diabetes, hyperlipidemia, and hypertension. Changes for each individual cognitive test, cognitive composites, ophthalmologic evaluations, and foods and nutrients ensuing intervention will be assessed by ANOVA and further by ANCOVA adjusting for the variables listed above. Statistical significance will be set at the *P* < 0.05 level. Analyses will be performed using SPSS software, version 16.0 (IBM Corp., New York, NY, USA).

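### The article is unclear on whether there are one or two primary outcomes, and sets a flat P < 0.05 with no success rule; if either of two can win, false-positive risk is up to 9.75%

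*Protocol article*

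**What the plan says.** All references are to the protocol article.

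- **Study Design** pairs the aims: "Primary aims are to assess changes in cognitive function and retinal integrity". The Abstract does the same.
- **Outcomes** carries the pair into the endpoints: "Primary outcomes are changes from baseline in the composite score of all neuropsychological tests for cognition and in the average thickness". The structure measured for the second outcome is then given: "of the retinal nerve fiber layer of each eye, as assessed by optical coherence tomography (OCT").
- **Cognitive testing**, after describing the global composite, uses the singular: "This composite was pre-specified as the primary outcome of the study". It then classes the separate cognitive domain composites as secondary.
- **Statistical Analyses** treats cognitive and retinal changes alike: "ophthalmologic evaluations, and foods and nutrients ensuing intervention will be assessed by ANOVA and further by ANCOVA adjusting for the variables listed above". The level follows: "Statistical significance will be set at the *P* < 0.05 level". Nothing is said about dividing it, ordering the tests or combining the two results.
- **Statistical Analyses** bases the sample size on one cognitive test, RAVLT total learning. The target is worded "In order to have a 90% power to detect differences in the contrast with the null hypothesis". The inputs to that calculation are set out as "assuming mean changes of 1.05 and 2.10 points in the control and intervention groups, respectively, with a standard deviation of 4.00". This gives 308 per group and 686 in total after 10% dropout.

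**The concern.** A reader cannot tell from the article whether RNFL thickness is a confirmatory endpoint. One section makes it co-primary. Another uses words that, taken literally, leave the composite as the trial's primary outcome.

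The flat significance level makes this matter. With two primary outcomes and no rule for combining them, nothing in the text stops a significant result on either one from being presented as a positive primary result. The chance of a false primary finding would then exceed the 5% of a single test. The contradiction also leaves room to treat RNFL as primary or not once its result is known.

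The article expects the results to count as high-level evidence and to inform public health policy, so the status of each endpoint should be fixed. The analyses are still written in the future tense although data collection has ended, so this can be settled before the cognitive and retinal comparisons are seen.

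**Working it through.** **1. Reproduce the planned sample size.** Inputs from Statistical Analyses: difference 2.10 − 1.05 = 1.05, SD 4.00, power 90%, level 0.05. Sidedness is not stated; two-sided is assumed.

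n per group = 2 × (1.960 + 1.282)² × 4.00² / 1.05² ≈ 305, against 308 stated. A one-sided test would give 249, so two-sided is the reading that fits.

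Power at 308 per group: the standard error is 4.00 × √(2/308) = 0.3223, and 1.05 / 0.3223 = 3.258. Φ(3.258 − 1.960) = 90.3%.

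Dropout: 308 / 0.9 = 342.2, rounded up to 343; 2 × 343 = 686, as stated.

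The plan therefore spends the full two-sided 0.05 on one cognitive test and allows nothing for a second primary test.

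**2. Chance of at least one false primary finding, if either outcome counts.** One test per outcome, each at two-sided 0.05, no true effect on either.

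- Independent tests: 1 − 0.95² = 9.75%.
- Correlated tests: 1 − P(|Z₁| < 1.96 and |Z₂| < 1.96), bivariate normal. The article gives no correlation, so a range is shown:

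| Correlation | Chance of at least one false finding |
|---|---|
| 0 | 9.75% |
| 0.1 | 9.7% |
| 0.3 | 9.5% |
| 0.5 | 9.1% |
| 0.7 | 8.3% |
| 0.9 | 7.0% |

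These figures count false findings in either direction. False claims of walnut benefit alone, for independent tests, are 1 − 0.975² = 4.9%.

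**3. The other readings.** With the composite as sole primary there is one primary test, so the error is 5%. If both must succeed, a false overall claim needs a significant result on at least one outcome with no true effect, so the error is at most 5%.

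**4. What a controlled procedure costs.** Holm compares the smaller p-value with 0.025 and, if that passes, the larger with 0.05. At the stricter step the planning calculation gives Φ(3.258 − 2.241) = 84.5% at 308 per group (84.4% with the t distribution). With the 636 completers reported under Anticipated Results, about 318 per group, the same calculation gives 85.7%.

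**The case against.** Four objections carry weight.

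- **No text says that a win on either outcome is enough.** The Abstract joins cognitive and retinal benefit with 'and'. This stands: a reader might infer an error rate of about 10% as a plain fact about the trial, but it is conditional on an either-wins rule that the article neither states nor excludes. Nor does the article state a family-wise rate, so it cannot be said to miss one.
- **'Only' does not appear in the Cognitive testing section.** In context the sentence may just rank the global composite above the domain composites. This is a fair reading, and it tells against demoting RNFL by default, since the Abstract, Study Design and Outcomes all pair cognition with retina. But the sentence refers to the whole study, so the two sections still need to be made to agree.
- **A multiplicity rule is often left to the analysis plan, which is not shown.** True, and its absence alone would be no finding. Here, however, the article itself names the primary outcomes inconsistently and states one undivided level covering cognitive and ophthalmologic changes. An unseen plan cannot make the two sections agree.
- **Two distinct questions might each be tested at 0.05 and reported separately.** Some statisticians defend this. If it is the intention, the article should say so and make no joint primary claim.

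Two further inferences are tempting but unsupported. The phrase about each eye might suggest three primary tests, with an error of about 12% to 14%. It may only describe the measurement; no text says the eyes are tested separately, and the figure depends on assumed between-eye correlations. A reader might also take 84% as the power for each primary endpoint. It rests on the RAVLT effect, and RAVLT total learning is neither primary outcome.

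**Conclusion.** The point holds as an internal inconsistency with a conditional consequence. Outcomes names two primary outcomes, Cognitive testing names one, and Statistical Analyses applies P < 0.05 throughout without a split, an order or a both-must-succeed rule.

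Depending on which reading is followed, the chance of a false primary finding runs from at most 5% (composite alone, or both required) to 9.75% (either counts, independent tests). For correlations of 0.1 to 0.5 the upper figure becomes about 9.7% to 9.1%. These figures assume two-sided testing, one test per outcome and no true effect on either; they count findings in both directions.

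The sample size is not wrong on its own inputs. No power figure can be given for RNFL or the composite, because the article gives no effect or SD for either.

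**What to change.** Before group comparisons on cognition and retina are seen, reconcile Outcomes with Cognitive testing by one of two routes, and state the choice in Statistical Analyses.

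1. **Both outcomes stay primary.** This fits the Abstract, Study Design and Outcomes best. Test the two with Holm at an overall two-sided 0.05. Define one RNFL value per participant, for example the mean of both eyes. In Cognitive testing, call the composite 'the primary cognitive outcome'.
2. **The composite is the sole primary outcome.** Say so under Outcomes, and test RNFL at 0.05 only after the composite is significant.

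**Cost.** Neither route needs new data. Under route 1 the stricter Holm step is 0.025, at which the RAVLT-based planning calculation has about 84% power instead of 90% at 308 per group. Route 2 leaves the level for cognition at 0.05, but RNFL cannot be claimed as confirmatory if the composite fails. It also downgrades an outcome that Outcomes declares primary, so it is a substantive change to be justified openly.

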##### Ophthalmologic evaluation

Retinal examinations were performed at baseline and end of the study by ophthalmologists (BCN) and trained technicians under the supervision of an ophthalmologist (LLU). The central and average thickness and volume of the macular neurosensorial retina and the thickness of the retinal nerve fiber layer were ascertained by OCT (Cirrus HD OCT, Zeiss, Germany).

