**FIGURE 1 F1:**
[figure not shown]
**Design of the Walnuts and Healthy Aging (WAHA) study**.

The pre-intervention visit with the study’s clinician lasted 1 h and consisted of a face-to-face interview with the candidate wherein complete information on the trial was provided, medical information was collected, inclusion/exclusion criteria were recorded, office blood pressure was measured, an ECG was performed, and the MMSE were administered. If the candidate was suitable for the trial and willing to participate, the informed consent was signed and blood extraction and urine collection and the first neuropsychologist and ophthalmologic visits were scheduled for next week. In the Barcelona site, one part of the informed consent concerned brain MRI, and candidates were asked to fill it in if willing to undergo the procedure. Once the pre-established number of 30% of the cohort was reached, no further candidates were offered brain MRI.

The neuropsychologist visit included the comprehensive test battery described in the Section “Cognitive Testing,” which took 90 min on average to complete. Whenever a cognitive alteration was detected at this visit, the candidate was excluded from further studies and was referred to the local Neurology clinic with a report describing the test findings. In the Barcelona site, the neuropsychologist provided full details on the brain MRI examination to willing candidates and scheduled the procedure.

In the ophthalmologic visit, which lasted approximately 30 min, a general history of eye health was taken and the OCT was performed. Any candidate found to have advanced AMD or bilateral cataracts precluding retinal examination was excluded from the study and referred to the local Ophthalmology clinic.

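### The retinal primary outcome is defined per eye, with no rule linking the two eyes; one value per participant should replace it.

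*Protocol article*

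**What the plan says.** The Outcomes section of the protocol article opens with the cognitive outcome, "Primary outcomes are changes from baseline in the composite score of all neuropsychological tests for cognition", and adds as its retinal counterpart the change "in the average thickness of the retinal nerve fiber layer of each eye". So the retinal variable is a primary outcome and is worded at eye level.

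The Ophthalmologic evaluation section says only that "the thickness of the retinal nerve fiber layer were ascertained by OCT". It does not say whether one eye is chosen, the two are averaged, or both are analysed.

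Statistical Analyses puts the eye data in the same sentence as everything else: "ophthalmologic evaluations, and foods and nutrients ensuing intervention will be assessed by ANOVA and further by ANCOVA adjusting for the variables listed above". One significance level, P < 0.05, applies throughout. No split between eyes and no term for the pairing of eyes is mentioned.

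Participants and Eligibility Criteria states that individuals were randomised, with couples treated as one unit. On eligibility at the eye visit, Stepwise Procedures (text under Figure 1) says: "Any candidate found to have advanced AMD or bilateral cataracts precluding retinal examination was excluded from the study".

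By contrast, the Carotid ultrasonography section, in its repeatability paragraph, says how right and left are combined for a secondary outcome: an average of the sides for mean IMT and the larger side for maximum IMT.

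**The concern.** Treatment is given to a person, who has two eyes. A per-eye variable therefore needs a rule that turns two measurements into one answer about the retina. The article states the variable per eye and names methods which, in their ordinary form, expect one independent observation per unit.

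On the literal reading there is a right-eye test and a left-eye test, each at 0.05. One eye could be significant and the other not, and the article does not say what would then be concluded. Taking whichever eye succeeds gives a false retinal claim more than 5% of the time. Each single-eye test also discards the information in the fellow eye, so precision is lost as well as error control.

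**Working it through.** **The plan's own figure.** The sample size rests on RAVLT, not the retina: difference 2.10 − 1.05 = 1.05, SD 4.00, power 90%, alpha 0.05 taken as two-sided.

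- n per group = 2 × (1.960 + 1.282)² × 4.00² / 1.05² ≈ 305 (306 with the t distribution), against 308 stated.
- With 10% dropout, 308/0.9 rounds up to 343 per group, and 2 × 343 = 686, as stated.

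The figure reproduces and counts participants. No calculation is given for the retinal outcome.

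**Inputs for the retinal check.** The test level of 0.05 is from Statistical Analyses. The 636 completers are from Anticipated Results, so there are at most 1,272 eyes. The between-eye correlation r of RNFL change is not in the document; I assume 0.3, 0.5 and 0.7. I also assume equal variance s² in the two eyes and both eyes readable.

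**(a) Each eye tested at 0.05, with success claimed if either is significant.** Under no effect the two test statistics are bivariate normal with correlation r, and the error is 1 − P(|Z₁| < 1.96 and |Z₂| < 1.96).

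**(b) Both eyes entered as independent observations.** The true variance of a person's two-eye mean is s²(1 + r)/2, but the analysis assumes s²/2. The standard error is therefore understated by a factor √(1 + r), and the true error is 2 × [1 − Φ(1.96/√(1 + r))]. At r = 0.5: 1.96/1.225 = 1.600, giving 11.0%.

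**(c) One two-eye mean per person.** The error is 5%. The standard error relative to a single-eye analysis is √((1 + r)/2). At r = 0.5 this is √0.75 = 0.866, about 13% smaller.

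| Assumed r | (a) either eye | (b) pooled as independent | (b) SE understated by | (c) two-eye mean | (c) SE against one eye |
|---|---|---|---|---|---|
| 0.3 | 9.5% | 8.6% | 1.14 | 5% | 0.806 (19% smaller) |
| 0.5 | 9.1% | 11.0% | 1.22 | 5% | 0.866 (13% smaller) |
| 0.7 | 8.4% | 13.3% | 1.30 | 5% | 0.922 (8% smaller) |

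For r as high as 0.9, (a) falls to 7.0% and (b) rises to 15.5%. Under (b), 1,272 eyes carry the information of 1,272/(1 + r) independent eyes: about 978, 848 and 748 at r = 0.3, 0.5 and 0.7.

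**If both eyes had to be significant**, the error would be 0.05 + 0.05 minus the value in (a): 0.10 − 0.0951 = 0.5%, 0.10 − 0.0907 = 0.9% and 0.10 − 0.0835 = 1.7% (rounded). The direction of the problem under separate testing thus depends on a decision rule that the article does not give.

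**The case against.** The strongest reply is that the article never says the faulty analysis will be done. A reader might infer that the outcome must be either tested twice or analysed with two correlated eyes counted as independent. The text does not support that either/or. A third route, one value per participant, fits ANOVA and ANCOVA without strain. Repeated-measures forms of these methods could also carry eye as a within-person factor. The full protocol or analysis plan, not shown here, may specify one of these.

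The pooling branch is the weaker inference. The sample size is in participants, the listed covariates describe people, and no count of eyes appears anywhere. The either-eye figures need a success rule that is not written down. All the sizes rest on an assumed correlation.

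It is also tempting to conclude from the bilateral-cataract wording that some participants contribute one eye and others two. That is possible, but it is inference: Participants and Eligibility Criteria separately excludes eye conditions that prevent ophthalmological evaluation, with no mention of both eyes, and nothing reports that one-eyed data exist.

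These objections limit the claim but do not remove it. The article does not merely leave a detail out: it defines a primary outcome at eye level. In OCT, average thickness most naturally means a summary within an eye, so the wording does not by itself supply averaging across eyes. A better definition is available, and the article's own handling of carotid sides shows that such a rule fits in a condensed account.

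**Conclusion.** The retinal primary outcome is defined on the wrong unit for a trial that randomises people, and no rule joins the two eyes. Taken literally, it yields two primary tests at 0.05. The retinal type I error would be about 8.4% to 9.5% for r from 0.7 down to 0.3 if success in either eye were claimed. It would be about 8.6% to 13.3% for r from 0.3 up to 0.7 if eyes were pooled as independent, which the document does not state. Both ranges are conditional on those routes and on the assumed correlations, and the article establishes neither route.

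What does not depend on a decision rule is that a two-eye mean is more precise than a single-eye analysis for any r below 1, given equal variances and the same effect in both eyes, and that it needs only one test. The point should be settled before the retinal results are analysed; the article still describes that analysis as to come. Clustering by couple is a separate issue and is not counted here.

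**What to change.** In Outcomes, replace the per-eye wording with one value per participant: the mean, over the two eyes, of the change from baseline in average retinal nerve fiber layer thickness, using the single evaluable eye if only one is readable. In Statistical Analyses, state that this value is tested once, by the planned ANCOVA, and that right and left eyes are reported descriptively without primary tests.

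The cost is a sentence in each section. No new measurements are needed, and the 686 stands because it was set on RAVLT. Participants with one readable eye would have a more variable value, s² against s²(1 + r)/2, so their number should be reported by group.
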